### Objectives

The primary objective for the CDCS is to determine the prevalence of VC in Chinese patients with CKD on HD or PD. The secondary objectives are:To test the hypothesis that a greater severity of baseline VC is associated with a higher risk for all-cause and CVD mortality, and non-fatal CV events in Chinese patients with CKD on HD or PD.To investigate the association between all-cause and CVD mortality, and non-fatal CV events and disease management (using serum levels of calcium, phosphorus and intact parathyroid hormone (iPTH), fibroblast growth factor 23 (FGF23) and related medications) in Chinese patients with CKD on HD or PD.To investigate the impact of current disease management on VC.To evaluate the control rate of patients achieving target goal of serum phosphorus, calcium and iPTH.To validate the cardiovascular calcification index (CCI) in Chinese patients with CKD on HD or PD.

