### Data collection

Visit 1 is at baseline/study entry and the follow-up includes 4 visits at 6 ± 1 month, 12 ± 1 month, 18 ± 1 months and 24 ± 1 month, respectively. The flow chart of detailed data and sample collection can be found in Table 3. At baseline, eligible patients will be evaluated for demographic information, smoking, alcohol drinking status, biochemical data, dialysis variables, concomitant medications, and personal and family disease history. Physical measurements including weight, height, body mass index (BMI) and vital signs (blood pressure and heart rate) will be obtained. Older age (male >55 years, female >65 years), arterial hypertension, family history (mother, father, brother, sister, children) of premature cardiovascular disease (≤55 years male, ≤65 years female), smoking, impaired glucose tolerance and/or impaired fasting glucose, dyslipidemia, and obesity are considered potent cardiovascular risk factors. The baseline biochemical data will be obtained using local routine laboratory methods performed within a week at the start of the study. If laboratory tests of serum 25-hydroxyvitamin D (25-OH Vit D) and FGF23 cannot be conducted in some centers, blood samples for testing 25-OH Vit D and FGF23 will be sent by the site study staff to those centers that can perform the assay. Blood sample collection will be performed according to the laboratory manual. Results from routine samples defined as samples taken within a week at the visit. Serum phosphorus, total calcium and iPTH will be tested at each visit. Target level of serum phosphorus, total calcium and iPTH in CKD stage 5 are defined according to Kidney Disease Outcomes Quality Initiative (K/DOQI) and KDIGO guidelines, respectively (Table 4) [20, 21]. Total serum calcium is adjusted if serum albumin is <4g/dL to better reflect the free calcium, using the formula proposed by the US Bone Metabolism Association: corrected total calcium (mg/dL) = total calcium (mg/dL) + 0.8 × [4.0 − serum albumin (g/dL)]. Date, time, primary reason and characteristics of death with autopsy results if applicable and any supportive documents that relate to fatal and nonfatal CV events are defined as clinical outcomes, and will be collected during the follow-up.

**Table 3 Tab3:** Study flow chart of the CDCS

Procedures	Visit time (month)				
	Baseline	6 ± 1	12 ± 1	18 ± 1	24 ± 1
Data release consent form	●				
Demography data	●				
Inclusion/exclusion criteria	●				

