Physical measurements (vital signs)	●				
Smoking and alcohol drink status	●				
Cardiovascular risk factors	●				
Disease history	●				
Concomitant medications	●	●	●	●	●
Hemoglobin, hematocrit	●				
Serum total calcium, phosphorus, iPTH	●	●	●	●	●
25-OH Vit D, FGF23	●		●		●
Glucose, HDL-C, LDL-C, TC and TG	●				
hs-CRP	●				
Serum albumin, ferritin, alkaline phosphatase	●				
Urea, uric acid, creatinine	●				
ABI	●				
Kt/V, dialysate calcium concentration	●				
Dialysis vintage, dialysis frequency and modality, membrane type	●				
EBCT or MDCT scan	●				●
Plain lateral lumbar radiograph	●				●
Echocardiography, LVMI/LVH	●				●
Clinical outcomes		●	●	●	●

*iPTH* Intact parathyroid hormone, *25-OH Vit D* serum 25-hydroxyvitamin D, *FGF23* Fibroblast growth factor 23, *HDL-C* High density lipoprotein-cholesterol, *LDL-C* Low density lipoprotein-cholesterol, *TC* Total Cholesterol, *TG* Triglyceride, *hs-CRP* High-sensitivity C-reactive protein, *ABI* Ankle-brachial index, *EBCT* Electron beam computed tomography, *MDCT* Multi-detector computed tomography, *LVMI* Left ventricular mass index, *LVH* Left ventricular hypertrophy

**Table 4 Tab4:** Target level of serum phosphorus, calcium and iPTH in CKD stage 5

Biochemical parameters	K/DOQI	KDIGO
Serum phosphorus	3.5–5.5 mg/dL (1.13–1.78 mmol/L)	Toward Normal [2.5–4.5 mg/dL (0.81–1.45 mmol/L)]
Corrected total calcium	8.4–9.5 mg/dL (2.10–2.38 mmol/L)	Maintain Normal [Healthy: 8.5–10.5 mg/dL (2.13–2.63 mmol/L)]
Serum iPTH	150–300 pg/mL (16.5–33.0 pmmol/L)	2–9 times the upper normal limit (65 pg/mL, 6.9 pmmol/L)

*K/DOQI* Kidney Disease Outcomes Quality Initiative, *KDGIO* Kidney Disease: Improving Global Outcomes, *iPTH* Intact parathyroid hormone

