### Secondary analysis

The key secondary analysis will be a comparison of survival (based on all-cause mortality) between patients with and without VC based upon the log-rank test performed at a significance level of 0.05. Hazard ratios and 95 % CIs will be calculated by a Cox proportional hazard regression model. In addition, the multivariable Cox proportional hazard regression model will be performed, using the stepwise method (*p* <0.05 as the inclusion criteria and *p* <0.10 as the exclusion criteria), considering with or without VC as the independent variable and the baseline variables with *p* <0.25 in univariate analysis as covariates, and hazard ratios and 95 % CIs for each factor will be presented. The same analyses will also be done for survival (based on CVD mortality) and non-fatal CV event free survival. For each of the above endpoints, the separate comparisons of patients with CAC, with AAC, with cardiac valve calcification to patients without VC will be made at a significance level of 0.05.

Association between disease management (including serum level of calcium, phosphorus and iPTH, and medications), 25-OH Vit D, FGF23, and all-cause/CVD mortality, non-fatal CV events will be identified with Cox proportional hazard regression model, considering disease management as the independent variables. Associations will be tested using the Wald test and described through the hazard ratios and 95 % CIs.

Association between disease management, 25-OH Vit D, FGF23, ankle-brachial index (ABI), and LVMI/LVH and the occurrence of CAC, AAC and cardiac valve calcification at baseline will be identified with the logistic regression model. The univariate logistic regression model will be performed separately, considering disease management, ABI, and LVMI/LVH as independent variables. Associations will be tested using the Wald test and described through the odds ratios and 95 % CIs.

Association between disease management, 25-OH Vit D, FGF23, ABI, and LVMI/LVH and severities (scores) of CAC, AAC and cardiac valve calcification at baseline will be identified with the linear regression model, considering disease management, ABI, and LVMI/LVH as independent variables.

Association between CAC progression and disease management, 25-OH Vit D, FGF23, ABI, as well as LVMI/LVH will be evaluated by ANCOVA as continuous variables and evaluated by ordinal multinomial logistic regression as categorical variables.

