In conclusion, as the first large-scale Chinese cohort study of patients with CKD on dialysis, the CDCS will utilize unique data for VC prevalence, demographic characteristics and disease management of the Chinese dialysis population to supplement the limitation of currently available data. The new results gained from the CDCS will provide increasing awareness of the importance of calcium balance and the risks of calcification, enable better clinical decisions and outcomes in assessing VC and management of serum phosphorus, calcium and iPTH in Chinese CKD patients on dialysis for nephrologists and health care providers, and be supportive for new clinical trials among Chinese CKD patients in the future. Further analysis of this cohort and comparison with other cohort studies in western countries might provide useful insight regarding race discrepancies on VC and related disease management in CKD patients.

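### Baseline dialysate calcium is collected but named in no regression of calcification on disease management, and the occurrence models are fixed as univariate

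*Protocol article*

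**What the plan says.** One secondary objective in the protocol article is to study how current disease management affects VC. The Objectives section describes management through "disease management (using serum levels of calcium, phosphorus and intact parathyroid hormone (iPTH), fibroblast growth factor 23 (FGF23) and related medications". The Secondary analysis section describes it again: "Association between disease management (including serum level of calcium, phosphorus and iPTH, and medications". Neither description mentions the dialysate.

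Three sets of models then relate calcification to management:
- **Occurrence at baseline** (CAC, abdominal aortic and valve calcification), by logistic regression: "The univariate logistic regression model will be performed separately, considering disease management, ABI, and LVMI/LVH as independent variables".
- **Severity scores at baseline**: the association "will be identified with the linear regression model, considering disease management, ABI, and LVMI/LVH as independent variables".
- **CAC progression** between the two scans, by ANCOVA and by ordinal logistic regression, with the same management variables, 25-OH vitamin D, FGF23, ABI and LVMI/LVH.

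Table 3 has a row for "Kt/V, dialysate calcium concentration" and a row that includes dialysis vintage and modality. Both are marked at baseline only. By contrast, "Serum phosphorus, total calcium and iPTH will be tested at each visit", and concomitant medications are also marked at all five visits.

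**The concern.** Dialysate calcium is set by the dialysis prescription, so it belongs to disease management in the ordinary sense. It can plausibly influence both serum calcium and calcification. If it does, a univariate odds ratio for serum calcium or for a calcium-related medication mixes that variable's own association with that of the dialysate. The same holds for modality, age, dialysis vintage and any other collected factor related to both sides.

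What is at stake is how the results for this objective are read. An unadjusted association could be reported as the impact of management on VC although the data to examine an obvious alternative explanation are already held. In the progression analysis, a change of dialysate or modality during the 24 months between scans would go unrecorded.

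**Working it through.** **1. Is there a plan figure to reproduce?** Not on this point. The only sample-size calculation concerns the log-rank comparison of survival. Its hazard ratio reproduces, ln(0.86)/ln(0.79) = 0.6398, but it has no bearing on the calcification models.

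**2. Collection set against use**

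| Item | Recorded (Table 3) | Named in the calcification regressions |
|---|---|---|
| Serum calcium, phosphorus, iPTH | baseline, 6, 12, 18, 24 months | yes, as disease management |
| Medications | baseline, 6, 12, 18, 24 months | yes, as disease management |
| 25-OH vitamin D, FGF23 | baseline, 12, 24 months | yes |
| ABI | baseline | yes |
| LVMI/LVH | baseline, 24 months | yes |
| Dialysate calcium | baseline | no |
| Modality, dialysis vintage | baseline | no |

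**3. What is fixed and what is open.** The logistic models are stated to be univariate and run separately, so they adjust for nothing. The linear, ANCOVA and ordinal models list predictors but state no adjustment set. For those, the text shows only that dialysate calcium is not named.

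**4. How large could the confounding be?** The documents give neither the correlation r between dialysate and serum calcium nor any effect b of dialysate calcium on calcification. Everything in this step therefore rests on assumed values.

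*Occurrence.* Suppose serum calcium has no effect of its own. For small effects, the apparent log odds ratio per SD of serum calcium is about r × b, where b is the log odds ratio per SD of dialysate calcium.
- r = 0.1, b = 0.1: 0.01, odds ratio 1.01
- r = 0.3, b = 0.2: 0.06, odds ratio 1.06
- r = 0.5, b = 0.3: 0.15, odds ratio 1.16

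If one of the two paths has the opposite sign, the product is negative and the range becomes exp(−0.01) = 0.99 to exp(−0.15) = 0.86. The direction is as open as the size.

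*Progression.* Assume a dialysate-to-serum path of 0.2 to 0.4 SD and a dialysate-to-progression path of 0.1 to 0.2 SD.
- Spurious slope: 0.2 × 0.1 = 0.02 SD to 0.4 × 0.2 = 0.08 SD.
- Patients with both scans: 1520 × 0.8 × 0.8 ≈ 973. This uses the plan's 20 % two-year mortality and 20 % loss, treats the two as independent, and assumes that everyone remaining is scanned.
- Standard error of a standardised slope: about 1/√973 = 0.032.
- Ratio: 0.02/0.032 = 0.6 to 0.08/0.032 = 2.5 standard errors.

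The assumed range therefore runs from negligible to enough to produce a nominally significant result.

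**5. Cost of adjustment in precision.** In a linear model, adding a covariate correlated r with serum calcium multiplies the standard error by about 1/√(1 − r²), before any gain from lower residual variance. This is 1.005 at r = 0.1, 1.05 at r = 0.3 and 1.15 at r = 0.5.

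**The case against.** Several objections are sound and limit the point.

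- **The variable is not excluded from every analysis.** A reader might infer that dialysate calcium is never set against VC. The section Demographic and baseline data analysis compares baseline data between the calcification groups and the group without VC, and dialysate calcium can be included there. The stepwise Cox model for VC and outcome screens baseline variables at p < 0.25 and could select it. However, neither analysis adjusts an estimate of serum calcium or medication against calcification.
- **The list is open and the article is condensed.** The Secondary analysis section introduces the components of management as examples, and covariates for the linear and progression models may stand in a fuller plan. This holds for those models. It does not rescue the logistic models, which the article itself fixes as univariate.
- **Confounding is not shown.** A reader might conclude that the serum-calcium results are confounded. Nothing in the documents links dialysate calcium to serum calcium or calcification, so they support only that confounding is possible and, in the univariate models, uncontrolled.
- **The calcium-balance sentence is not an inference.** The Discussion expects "increasing awareness of the importance of calcium balance and the risks of calcification". It is tempting to call this an unsupported conclusion, but it is a hoped-for benefit and not an objective, endpoint or planned estimate.
- **Adjustment may be wrong in part.** If dialysate calcium is chosen in response to serum calcium, it lies downstream, and adjusting for it could remove part of the association of interest. This stands, and is why both sets of estimates are needed.
- **One covariate is singled out.** Univariate models omit all confounders. This widens the point, and dialysate calcium is one specific, already collected example.
- **Repeat collection is a design preference.** Recording an item once, in patients on stable dialysis, is a limitation and not an error. The point does not depend on changing it.

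**Conclusion.** The point holds as an analysis weakness of modest cost and unknown size. Dialysate calcium is collected, is a managed exposure, and is named in no regression of calcification occurrence, severity or CAC progression on disease management. The occurrence models are explicitly unadjusted. Followed as written, they yield serum-calcium and medication associations that may be confounded by dialysate calcium, modality and other collected baseline factors.

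Neither size nor direction can be derived from the documents. The odds ratios and the multiples of the standard error in the working illustrate assumed path sizes and estimate nothing about this cohort. For the linear and progression models, the conclusion is weaker: dialysate calcium is not named, and the adjustment set is unstated. The point concerns analysis and reporting only and implies nothing about the choice of dialysate.

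**What to change.** 1. Keep the univariate logistic models as a first step and supplement them with multivariable models.
2. In the logistic, linear and CAC-progression models, include baseline dialysate calcium as a disease-management predictor, alongside modality and other collected baseline factors such as age and dialysis vintage.
3. Report the serum-calcium and medication estimates with and without dialysate calcium, and explain that it may be a response to serum calcium as well as a cause of it.
4. State as a limitation of the progression analysis that dialysate calcium and modality are recorded only once, so later changes are not captured.

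No new measurement is needed, because the baseline values are already in the data set. The cost is some additional modelling and somewhat wider intervals, depending on how strongly dialysate and serum calcium are correlated. Repeating the two items at follow-up visits would be optional. It would need new fields in 24 centers of a study already recruiting, and this fix does not depend on it.

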## Methods/Design

### Study design

The CDCS is a national, multicenter, non-interventional, 24 month prospective cohort survey in CKD patients on dialysis. The study includes a baseline visit and 4 other visits at 6 month intervals. The estimated enrollment period is 10 months. It is planned to consecutively recruit 1520 patients with ESRD receiving stable hemodialysis (HD) or peritoneal dialysis (PD) for at least 6 months in 24 dialysis centers in China. Participating centers will be selected based on logistics constraints. Consecutive patients who fulfill the inclusion and exclusion criteria and are willing to participate will be included in the study (Table 1). Written informed consents were obtained from all patients before participation. Each site is expected to enroll approximately 30 patients. After that, enrollment will be competitive at all sites. This study will be able to mirror real life management of these patients. All statistical analyses will be performed using SAS 9.2 software (SAS Institute, Cary, NC, USA). All hypothesis tests will use two-sided tests with a significance level of 0.05.

**Table 1 Tab1:** Inclusion and exclusion criteria of the CDCS

Inclusion criteria	Exclusion criteria
Male or female patients ≥18 years old	Patients’ life expectancy <6 months
Patients with ESRD receiving stable HD or PD for at least 6 months	Patients with acute kidney injury, active inflammatory diseases, parathyroidectomy or evident malignancies
Patient or legally accepted representative willing to sign Data Release Consent Form.	Patients with conditions making arterial calcification measurements technically impossible or unreliable, such as cardiac arrhythmias, amputations or severe peripheral vascular lesions
	Concomitant diseases that affect calcium status and soft tissue calcifications (sarcoidosis, multiple myeloma, HIV, amyloidosis)
	Pregnant or lactating women or women planning to become pregnant in the 6 months following entry into the study

*ESRD* End-stage renal disease, *HD* Hemodialysis, *PD* Peritoneal dialysis, *HIV* Human immunodeficiency virus

CKD is defined as abnormalities of kidney structure or function, present for >3 months, with implications for health, according to Kidney Disease: Improving Global Outcomes (KDIGO) 2012 Clinical Practice Guideline for the Evaluation and Management of CKD (Table 2) [19].

**Table 2 Tab2:** Criteria for CKD (either of the following present for >3 months)

	Criteria

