### Imaging methods

VC images will be taken within a week of enrolment and the final visit of the study. Coronary artery calcification (CAC), abdominal aortic calcification (AAC) and cardiac valve calcification will be assessed by electron beam computed tomography (EBCT) or multi-detector computed tomography (MDCT), plain lateral lumbar radiograph and echocardiography, respectively. In addition, results of left ventricular mass index (LVMI) and left ventricular hypertrophy (LVH) through echocardiography will be taken within a week of enrolment and the final visit of the study as well.

CAC is measured by EBCT or MDCT as originally described by Agatston et al. [22]. Thirty to forty contiguous tomographic slices will be obtained at 3-mm intervals beginning 1 cm below the carina and progressing caudally to include the entire coronary tree. An attenuation threshold of 130 Hounsfield units (HU) and a minimum of 3 contiguous pixels will be used for identification of a calcific lesion. The density factor is assigned in the following manner: 1 for lesions with peak attenuation of 130–199 HU, 2 for lesions with peak attenuation of 200–299 HU, 3 for lesions with peak attenuation of 300–399 HU, and 4 for lesions with peak attenuation >400 HU [22]. Total CACS is determined by summing individual lesion scores from each of four anatomic sites (left main, left anterior descending, left circumflex, and right coronary artery). The CACS will be divided into approximate tertiles (0, <100, ≥100, ≥400 and ≥1000). CAC progression is evaluated as a continuous variable by calculating the difference in Agatston score between the two CT scans divided by the time between imaging. The 2-year progression of CAC is categorized as follows: absent (≤25th percentile), moderate (25th-75th percentiles), and accelerated (≥75th percentile).

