### Determination of sample size

From the latest published annual data, the mortality rate of Chinese CKD dialysis patients is approximately 10 %, so we assume the 2-year mortality rate for Chinese CKD dialysis patients is around 20 % [24]. Assuming the ratio between patients with and without VC is 7:3, a two-sided log rank test with an overall sample size of 1520 subjects (of which 1064 are in the VC group and 456 are in the non-VC group) achieves 80 % power at a 0.05 significance level to detect a difference of 0.07 between 0.79 and 0.86—the proportions surviving in VC groups and without VC group, respectively. This corresponds to a hazard ratio of 0.6398. The proportion of patients lost during follow-up is predicted to be 20 %. These results are based on the assumption that the hazard rates are proportional. Therefore, 1520 subjects are to be recruited.

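### The CAC progression models do not name the baseline CAC score, so existing calcification can be reported as progression; stating that it enters both models is a cheap improvement

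*Protocol article*

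**What the plan says.** All references are to the Protocol article.

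- **Outcome (Imaging methods).** Continuous CAC progression is obtained by "calculating the difference in Agatston score between the two CT scans divided by the time between imaging". It is an absolute change per unit time. The three progression categories are cut at the 25th and 75th percentiles of 2-year progression. Neither form is conditioned on the starting score. The severity cut-points in the same section run from 0 to 1000 and above.
- **Models (Secondary analysis).** "Association between CAC progression and disease management, 25-OH Vit D, FGF23, ABI, as well as LVMI/LVH will be evaluated by ANCOVA as continuous variables", and progression is also to be "evaluated by ordinal multinomial logistic regression as categorical variables". The sentence names markers and model types. It neither names baseline CAC nor says that it is left out.
- **Same markers at baseline (Secondary analysis).** The association of the same markers with "severities (scores) of CAC, AAC and cardiac valve calcification at baseline will be identified with the linear regression model".
- **Availability (Table 3).** A CT scan is scheduled at baseline and at month 24, so every patient with a progression value has a baseline score.
- **Testing (Study design).** "All hypothesis tests will use two-sided tests with a significance level of 0.05".

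**The concern.** The Agatston score has no ceiling, so patients who start near 0 and patients who start above 1000 may differ in how many units they gain over two years. If they do, the starting score predicts the absolute change. A marker that merely accompanies heavy calcification at entry will then correlate with the change, even if it has no bearing on how fast calcification advances. The plan itself treats such marker-baseline associations as plausible, since it sets out to test them.

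Among the secondary objectives is the impact of current disease management on vascular calcification. The CAC progression analysis is the only longitudinal analysis the article states for it; the other analyses of that question are cross-sectional at baseline. Without the starting score, the longitudinal analysis may partly repeat the cross-sectional one under the name of progression. The primary prevalence estimate and the key secondary survival comparison are not affected.

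**Working it through.** **1. The plan's own figure.** The article gives no sample size or power for the progression analysis. Its only calculation is for the log-rank comparison, and that reproduces:

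- Hazard ratio = ln(0.86)/ln(0.79) = 0.6398.
- Events by Freedman's formula with φ = 3/7: (1.960 + 0.842)² × (1 + φ × 0.6398)² / [φ × (1 − 0.6398)²] = 229.2.
- Overall death proportion = 0.7 × 0.21 + 0.3 × 0.14 = 0.189. Then 229.2/0.189 = 1212.6, and 1212.6/0.8 = 1516, against the stated 1520.

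This does not bear on the point, but it supplies the 1520 patients, 20 % loss and about 20 % two-year mortality used below.

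**2. Patients with two scans (assumption).** 1520 × 0.8 alive × 0.8 not lost = 972.8, about 973. As a range I use 912 (1520 × 0.6, both losses subtracted) to 1216 (1520 × 0.8, only one applied).

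**3. False-positive rate without baseline CAC, baseline measured without error.** Take a marker with no effect on progression. Its induced correlation with change is r = r(marker, baseline) × r(baseline, change). The two-sided 5 % rejection rate by Fisher's z is approximately Φ(atanh(r) × √(N − 3) − 1.960). Both correlations are assumptions.

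| marker-baseline | baseline-change | r | rejection, N = 973 |
|---|---|---|---|
| 0.1 | 0.5 | 0.05 | 34.4 % |
| 0.2 | 0.3 | 0.06 | 46.5 % |
| 0.2 | 0.5 | 0.10 | 87.8 % |
| any | 0 | 0 | 5 % (nominal) |

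For the third row: atanh(0.10) × √970 = 3.125, and Φ(3.125 − 1.960) = 0.878. With N = 912 it is 85.7 %, and with N = 1216 it is 93.8 %.

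**4. With and without baseline CAC, allowing for scan error.** This is a simulation of linear models with 972 patients and 600 runs per case. True baseline T is standard normal, the marker has correlation ρ with T, and true change is bT plus noise with total variance 1. Scan error of variance (1 − reliability)/reliability is added to each scan. The Monte Carlo standard error at 5 % is √(0.05 × 0.95/600) = 0.9 points.

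| b | ρ | reliability | rejection without baseline | with baseline |
|---|---|---|---|---|
| 0 | 0.3 | 1.0 | 5.5 % | 6.0 % |
| 0 | 0.3 | 0.9 | 4.8 % | 16.8 % |
| 0.3 | 0.1 | 1.0 | 15.3 % | 5.5 % |
| 0.3 | 0.1 | 0.9 | 13.7 % | 7.8 % |
| 0.3 | 0.3 | 1.0 | 77.3 % | 5.7 % |
| 0.3 | 0.3 | 0.9 | 72.0 % | 20.3 % |
| 0.5 | 0.3 | 0.9 | 98.3 % | 28.2 % |

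**5. When adjustment helps.** In that model the bias of the marker coefficient is bρ without baseline. With it, the bias is ρm(1 + b)/(1 + m − ρ²), where m is the scan-error variance. At reliability 0.9, m = 0.1/0.9 = 0.111. For b = 0.3 and ρ = 0.3 the two biases are 0.3 × 0.3 = 0.090 and 0.3 × 0.111 × 1.3/(1 + 0.111 − 0.09) = 0.042; the simulated means are 0.091 and 0.043. For b above 0 the biases are equal at b = m/(1 − ρ²) = 0.111/0.91 = 0.12. Above that, adjustment has the smaller bias; below it, the larger.

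**6. Precision.** Without scan error, the standard error of the marker slope falls from 0.0321 to 0.0278 at b = 0.5, ρ = 0, but goes from 0.0320 to 0.0321 at b = 0.3, ρ = 0.3. The gain disappears in the setting where confounding matters.

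These figures are for the linear model. The ordinal model was not simulated; the same mechanism applies, but its size was not computed.

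**The case against.** **The omission is read from silence.** The sentence names the exposures of interest and two model types. It does not present a closed covariate list, and a condensed article commonly leaves covariates to the full protocol or analysis plan. ANCOVA by name carries covariates, and where the same section wants univariate models (the baseline logistic regressions) it says so. This stands to the extent that a reader might infer that the plan deliberately excludes baseline CAC; the article does not say that. It does not remove the point. The continuous markers alone would satisfy the label ANCOVA, nothing comparable is said of the ordinal model, and the multivariable Cox model in the same section is described down to its entry and exit thresholds. Run as written, the progression models contain no baseline term.

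**Adjusting change for baseline is not a general rule in observational data.** Patients have been on dialysis for at least 6 months at entry, so earlier management may have shaped baseline CAC. Change and baseline-adjusted change then answer different questions. This stands, and it is a reason to report both.

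**Adjustment can itself create bias.** This also stands: 16.8 % against 4.8 % when progression is unrelated to an error-prone baseline (b = 0, ρ = 0.3, reliability 0.9). The harm is confined to weak dependence on baseline. At b = 0.3 with the same ρ and reliability the comparison is 20.3 % against 72.0 %.

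**Stronger readings.** A reader might infer that the markers will appear as drivers of progression, that the accelerated group will mostly be patients with heavy calcification at entry, or that power is materially lost. The article gives no correlation or distribution that would support any of these as a fact, and the precision gain largely vanishes when the marker tracks baseline.

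**Conclusion.** The point holds as a low-cost improvement, not as a demonstrated error. The article names the markers for both CAC progression models, does not name baseline CAC, and defines progression as an absolute change per unit time that is not conditioned on the starting score. If progression depends on that score and a marker correlates with it, the models as written can present existing calcification as progression.

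Under the assumed correlations and about 973 two-scan patients, the false-positive rate for a null marker runs from about 34 % to 88 %. It stays at the nominal 5 % if either correlation is zero. The conclusion rests on those assumed correlations, on the assumed number of patients with two scans, and on a linear model. Confounding by existing calcification is the reason to act; precision is not.

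**What to change.** In the Secondary analysis section, state that the baseline CAC score enters both the ANCOVA and the ordinal logistic model of CAC progression. It could enter as ln(CACS + 1), or as mutually exclusive groups built from the article's own cut-points: 0; above 0 to below 100; 100 to below 400; 400 to below 1000; 1000 and above. Report the same models without baseline CAC alongside as a sensitivity analysis. If the full protocol or analysis plan already does this, a sentence saying so is enough.

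The cost is a change of wording and one covariate already scheduled for collection, with no new visit or scan. The downside is that scan error in the baseline score enters both the covariate and the change. Adjustment therefore leaves some bias, and can add some if progression is unrelated to baseline. The two sets of results should be read together. Their difference does not by itself separate confounding from measurement error, and the text should say so.
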